#### Focus Groups

Each participant country will carry out at least 5 focus groups with hospital workers enrolled and not enrolled in the course. Participants will be volunteers. The focus groups will consist of homogenous working categories to avoid possible reticence of some participants to openly talk in the presence of their supervisors. In each country focus groups will be conducted by external local qualitative researchers that will follow the same protocol.

### Data Analysis

Descriptive statistics will be used for the quantitative indicators. The quantitative variables will be summarized using means and other central tendency measurements, whereas the qualitative data will be summarized by computing their frequencies and percentages. The qualitative indicators gathered by the qualitative methods (focus groups and interviews) will be summarized using the classical content analysis approach (creating codes and chunks of information and the researcher complements the codes with description of this code). Analysis of the data will be validated by informants to increase the reliability of the data [41].

Usual statistics will be used to describe the sample and non-parametric tests will be used for pre-post comparisons for tobacco control policies (measured by Tool 1) and the trainees’ knowledge, attitudes, and behaviors (measured by the Tool 2). In addition, a validity and reliability test of both instruments is planned.

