**Methods:**

This study will use a mixed-methods design with a pre-post evaluation (quantitative approach) and in-depth interviews and focus groups (qualitative approach). The main outcomes will be (1) participants’ attitudes, knowledge, and behaviors before and after the training; and (2) the level of implementation of tobacco control policies within the hospitals before and after the training.

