### Hypothesis

Our primary hypothesis is the participants in the online tobacco cessation training program will increase their tobacco-related knowledge, attitudes, and behaviors by the 6-month follow-up, as compared to baseline conditions prior to the training. Our secondary hypothesis is that participating hospitals will exhibit greater tobacco control progression, commitment, and implementation of tobacco cessation services.

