## Methods

### Study Design

The Fruitful Study is a 2-year mixed-method (qualitative and quantitative) study conducted in one hospital in each of the three participant countries (Bolivia, Guatemala, and Paraguay).

For the quantitative approach, a pre-post design will be used to (1) assess participants’ attitudes, knowledge, and behaviors before and after the training using a questionnaire (Tool 1); and (2) measure the level of implementation of tobacco control policies within the participant hospitals before and after the training using the Self-Audit Questionnaire (SAQ) (Tool 2). For the qualitative approach, focus groups and in-depth interviews of key persons will be used. With this methodology we aim to (1) explore the experience of adapting the training program in each of the participant hospitals; (2) ascertain participants’ experience undertaking the training program; and (3) understand the opportunities and barriers of undertaking online smoking cessation training programs in the participant countries. With the results of the focus groups, the research team aims to identify any difficulties in accessing and completing the course and to make the necessary improvements.

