### Instruments

#### Tool 1

To assess differences in tobacco control polices implemented within the hospitals we will use the European Network of Smoke free Hospitals (ENSH) SAQ [35]. This tool was developed for the ENSH-Global Network for Tobacco Healthcare Services. The questionnaire is composed of the following 10 policy standards: (1) commitment (6 items); (2) communication (4 items); (3) education and training (4 items); (4) identification and cessation support (8 items); (5) tobacco control (5 items); (6) environment (6 items); (7) healthy workplace (5 items); (8) health promotion (1 item); (9) compliance monitoring (2 item); and (10) and policy implementation (1 item). Each item is scored 1 (not implemented), 2 (less than half of the aspects are implemented), 3 (more than half are implemented), or 4 (fully implemented). The maximum score of the ENSH SAQ is 168 points, calculated as the sum of the 10 standards [35]. At baseline, the SAQ provides information on the tobacco control policies undertaken within the organization. Once it is used to monitor the project, the instrument detects the fulfilled standards and the areas for improvement.

#### Tool 2

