## Discussion

### Principal Findings

We will consider a good level of coverage of the training program if at least 50% of the enrolled health professionals in each hospital conclude the training program. We will measure the engagement of the training program with the focus groups and key informant interviews. We anticipate that hospitals will increase their tobacco control policies by 20% to 30% according to the SAQ. In addition, we anticipate that health professionals’ level of knowledge, attitudes, and perception in tobacco cessation will increase to 30% to 40%.

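### The planned pre-post test of the hospital policy score rests on three hospitals, so its smallest attainable exact p is 0.25 whatever the effect

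*Protocol article*

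**What the plan says.** The Study Design section describes a "study conducted in one hospital in each of the three participant countries (Bolivia, Guatemala, and Paraguay"). The Hypothesis section makes the hospital the subject of the second hypothesis: "Our secondary hypothesis is that participating hospitals will exhibit greater tobacco control progression, commitment, and implementation of tobacco cessation services". The Methods part of the abstract lists the same outcome among the main ones: "the level of implementation of tobacco control policies within the hospitals before and after the training".

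The Instruments section describes the SAQ as an audit of the organisation that is summed to a single total: "The maximum score of the ENSH SAQ is 168 points, calculated as the sum of the 10 standards". The Data Analysis section states that "non-parametric tests will be used for pre-post comparisons for tobacco control policies (measured by Tool 1"). It does not name the test or the unit of analysis. It adds that "a validity and reliability test of both instruments is planned", without naming a sample. The Discussion gives the expected size of change: "We anticipate that hospitals will increase their tobacco control policies by 20% to 30% according to the SAQ".

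The tool labels are swapped in one place. Study Design calls the SAQ Tool 2, while Instruments calls it Tool 1. The Data Analysis sentence names tobacco control policies and follows the Instruments labelling, so there is no doubt that it means the SAQ.

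**The concern.** A non-parametric paired test draws its p-value from the ways in which the signs (or signed ranks) of the changes could have fallen. With very few pairs there are very few ways, and even the most favourable outcome is not rare under the null. Three hospitals are too few for such a test to reach any customary significance level, however large the improvement.

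A stated hypothesis, whose outcome the abstract ranks among the main ones, is therefore attached to a test whose verdict is fixed in advance. Non-significance would be certain and uninformative, yet could be reported as absence of change. Because the article does not fix the unit, an analyst could also turn to the items or standards as observations. That would give a small p without supporting any inference about hospitals.

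**Working it through.** **Inputs**

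- Hospitals: 3 (Study Design; Table 1).
- SAQ: 10 standards with 6, 4, 4, 8, 5, 6, 5, 1, 2 and 1 items, each scored 1 to 4 (Instruments).
- Anticipated SAQ gain: 20% to 30% (Principal Findings).
- Alpha .05, beta .1: stated in Sample Size, for the participant-level comparison only. Using .05 for the SAQ is an assumption.
- One SAQ total per hospital per time point: the natural reading of Instruments, but not stated outright.

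**The article's own figures.** The items sum to 6+4+4+8+5+6+5+1+2+1 = 42, and 42 × 4 = 168, which agrees with the stated maximum. The sample size of 43 per hospital (3 × 43 = 129) counts trainees. The article gives no sample size or power for the hospital-level comparison, so there is no hospital-level figure to reproduce.

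**Exact paired tests with three hospitals**

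- Number of sign patterns: 2^3 = 8, equally likely under the null.
- Signed-rank sums over the 8 patterns: 0, 1, 2, 3, 3, 4, 5, 6. Only one pattern, in which all three improve, reaches 6.
- One-sided p = 1/8 = 0.125. Two-sided p = 2/8 = 0.25.
- The sign test gives the same values: (1/2)^3 = 0.125 and 2 × (1/2)^3 = 0.25.

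The size of the gain does not enter. A rise of one point in each hospital and a rise of 30% in each give the same p. Power at .05 is therefore exactly zero.

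**How many hospitals would be needed.** With n pairs, all improving, the two-sided minimum is 2 × (1/2)^n:

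| Hospitals | Two-sided | One-sided |
|---|---|---|
| 3 | 0.25 | 0.125 |
| 4 | 0.125 | 0.0625 |
| 5 | 0.0625 | 0.031 |
| 6 | 0.031 | 0.016 |

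A p below .05 first becomes possible with six hospitals two-sided or five one-sided, and only if every one improves.

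**Does another choice of test help?**

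- Normal approximation to the signed-rank test, uncorrected: mean 3, variance 3×4×7/24 = 3.5, z = (6 − 3)/√3.5 = 1.60. This gives p = 0.109 two-sided and 0.054 one-sided, still above .05.
- Mann-Whitney 3 v 3, ignoring the pairing: C(6,3) = 20 arrangements, so the exact minimum is 2/20 = 0.10 two-sided and 1/20 = 0.05 one-sided. Neither is below .05.
- Only large-sample approximations to that unpaired test fall below .05 (two-sided 0.0495 uncorrected; one-sided 0.040 corrected, 0.025 uncorrected). They ignore the pairing and are not valid at this size.

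**Items or standards as units.** Ten standards all improving would give 2 × (1/2)^10 = 0.002. Items would raise the nominal number of observations from 3 to 42 × 3 = 126. These are correlated answers about the same three organisations, so the effective replication for a statement about hospitals remains three.

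**Reliability, if it rested on these hospitals alone.** The F-based 95% interval for Cronbach's alpha with n units and k = 42 items has limits 1 − (1 − α)·F at the .975 and .025 quantiles, on n − 1 and (n − 1)(k − 1) degrees of freedom. For an assumed observed alpha of 0.80, n = 3 gives about 0.23 to 0.99. Counting the two time points as six independent units, which they are not, still gives 0.47 to 0.97.

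**The case against.** The strongest reply is that the article is condensed and that the full protocol or analysis plan may name the test and the unit. That does not rescue the sentence, because no later choice of test adds hospitals. It does limit what can be claimed, and several stronger readings fail on the text.

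- **Significance level.** A reader might infer that the plan tests the SAQ at .05. Alpha is given only in Sample Size, for trainees, so .05 is an assumption here. A floor of 0.25 (0.125 one-sided) would miss a .10 level as well.
- **One score per hospital.** The article does not say who completes the SAQ or how many forms are returned. One total per hospital is the natural reading of an organisational audit, and several raters would still leave three hospitals.
- **Only two outcomes, both wrong.** A reader might infer that the plan must end in either an empty non-significant result or a spurious significant one. Data Analysis also promises descriptive statistics for the quantitative indicators, so the SAQ changes can be reported properly beside the test. Nothing says that items or standards will serve as units; that route is left open, not planned.
- **Reliability on three hospitals.** A reader might infer that the SAQ validity and reliability test uses only these three hospitals. The article describes no other SAQ data source, but it names no sample, raters or type of validity. Content validity or outside SAQ data are not excluded.
- **The education and training standard.** A reader might want the SAQ total shown without it, on the ground that delivering the course could raise its four items. The article gives no item wording and defines the total over all ten standards. The question has no bearing on the number of hospitals, so no such analysis is requested.

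**Conclusion.** The point holds in its narrow form. The planned non-parametric pre-post comparison of the SAQ cannot support the secondary hypothesis: with three paired hospitals the exact p cannot fall below 0.25 two-sided or 0.125 one-sided, and power at .05 is zero even if all three gain the anticipated 20% to 30%. This rests on two assumptions: the hospital is the unit with one SAQ total per time point, and the customary .05 level applies. The first follows naturally from the hypothesis and the instrument; the second makes little difference, given how high the floor is. Moving to items or standards as observations would not be a valid way out.

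The primary, participant-level comparison is not affected. The remark about SAQ reliability is conditional on the test resting on these three hospitals alone, which the article does not state.

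**What to change.** In Data Analysis, remove the SAQ from the sentence on non-parametric tests and keep that sentence for the trainee questionnaire. Add wording such as:

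> The SAQ outcome is descriptive. For each of the three hospitals we will report the baseline score, the follow-up score and the change, for the total and for each of the 10 standards, and will compare these with the anticipated 20% to 30% increase. No significance test will be done. Items and standards will not be treated as independent units.

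Reword the secondary hypothesis, or its interpretation, to match. State what the 20% to 30% is a percentage of, so that the comparison can be made.

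For validity and reliability, state the SAQ sample. If it is only these three hospitals, limit the test to the trainee questionnaire or name a larger set of hospitals for the SAQ.

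The cost is a few sentences, with no new data and no change to conduct. All that is given up is a p-value that could not have fallen below 0.25. The article was written while follow-up data were still being collected, so the change is best made before the follow-up SAQ results are examined.

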### Sample Size

Based on literature regarding gains of training [27,40], we anticipate an increase of 40% in health professionals’ level of knowledge, attitudes, and perception in tobacco cessation from baseline to 6 months. Given this estimate, we will need a minimum of 43 participants per hospital, (total 129, alpha=.05, beta=.1, and 15% dropouts). However, we expect at least an overall enrollment of 300 professionals (100 per hospital).

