This online training program includes (1) slides; (2) review exercises; (3) cases of 4 patients differing in demographics, diagnostic, stages of change, setting; and (4) problem solving exercises. The training provides several materials including slides, online tutorials with an expert tutor, recommended readings, patient cessation brochures, a therapeutic pocket guideline, and an organizational recommendation model to facilitate the implementation of tobacco cessation services in the hospital setting.

The original online course was firstly tested by 10 voluntary participants in Catalonia (Spain). Evaluation of the tobacco cessation program was thereafter tested in the ICO by 150 health professionals. This pilot test proved the acceptability of the training model, the adequacy of its contents, and obtained a high level of satisfaction in the trainees. This training initiative has also been shown to increase the level of implementation of tobacco control in Catalan hospitals (according to the SAQ) [35] and the engagement of health professionals [36,37], thus making them part of the solution. This course has been accredited by the Council of Oncology in Europe (ACOE) in support of Continuing Medical Education for physicians. Since its launch in November 2012 to June 2014 more than 1000 Catalan health professionals have taken this course.

Based on literature regarding attrition among online learners [38], and our own experience delivering online training to Catalan health workers, we anticipate that roughly 50% of participants will complete all components of the proposed activities.

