## Results

We have enrolled 281 hospital workers (105 from Bolivia, 88 from Guatemala, and 88 from Paraguay). The overall average completion rate is 66.2% (186/281). At the time of submission of this paper, data collection for the post-evaluation was underway. Evaluations will finish in November 2016 and results are expected by the beginning of 2017. Results of this study will be reported in two follow-up papers: one about the formative evaluation and the other about the summative evaluation.

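### The minimum of 43 per hospital allows for 15% loss although the article expects about half to complete, so that minimum does not carry its stated 90% power (minor; actual enrollment covers it)

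*Protocol article*

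**What the plan says.** The Sample Size section of the protocol article starts from an anticipated gain ("we anticipate an increase of 40% in health" professionals' knowledge, attitudes and perception) and arrives at a "minimum of 43 participants per hospital, (total 129, alpha=.05, beta=.1, and 15% dropouts". It then contrasts this minimum with the enrollment it hopes for: "we expect at least an overall enrollment of 300 professionals (100 per hospital".

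Three other places bear on attrition:

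- Selecting a Suitable and Effective Training Program, citing literature on online learners and the team's own courses: "we anticipate that roughly 50% of participants will complete all components of the proposed activities".
- Principal Findings, which defines good coverage: "at least 50% of the enrolled health professionals in each hospital conclude the training program".
- Results: "The overall average completion rate is 66.2% (186/281", with enrollment given as "We have enrolled 281 hospital workers (105 from Bolivia, 88 from Guatemala, and 88 from Paraguay".

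Under Instruments (Tool 2), the post-training questionnaire is sent three months after a participant finishes the course. The Data Analysis section plans non-parametric pre-post comparisons. The term dropouts is not defined, and the 15% is nowhere related to the 50%.

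**The concern.** The individual-level hypothesis is a change within participants, so each evaluable participant needs both a baseline and a post-training questionnaire. The second questionnaire is timed from finishing the course, so the number who finish is the natural ceiling on the number of pairs. Any non-response at three months lowers it further.

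A minimum that allows for 15% loss therefore conflicts with an expectation that about half will finish. A hospital that enrolled exactly 43 would be declared to have 90% power when, on the authors' own attrition figure, it would not. What is at stake is the correctness of the stated threshold, which the summative paper or a similar online-training study might reuse.

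**Working it through.** **Inputs.** From Sample Size: alpha 0.05, power 90%, 15% dropouts, 43 per hospital, 129 in total. From the training-program section: 50% completion. From Results: 186/281 = 66.2% completion; enrollment 105, 88, 88. Not given: SD, baseline level, specific test, sidedness, and whether the 40% gain is relative or absolute.

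**Step 1: the article's own figure.** The full calculation cannot be reproduced without the missing inputs, but the dropout step can. With n/(1 − d), 36/0.85 = 42.4, rounded up to 43, and 3 × 43 = 129. In the other direction, 43 × 0.85 = 36.55. So 43 stands for about 36 evaluable pairs per hospital, or 37 if the inflation was n × (1 + d).

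**Step 2: pairs left from 43 enrolled.**
- At 50% completion: 43 × 0.50 = 21.5, so 21 to 22 pairs.
- At 66.2% completion: 43 × 0.662 = 28.5, so about 28 pairs.

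**Step 3: power at those numbers.** Take the effect to be whatever gives 90% power at 36 pairs. In the two-sided normal approximation, the standardised effect is (1.960 + 1.282)/√36 = 0.540, and power at n pairs is Φ(0.540√n − 1.960):
- n = 21: 0.697
- n = 22: 0.717
- n = 28: 0.816
- n = 36: 0.900 (by construction)

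Other tests, at 21 to 22 pairs:
- Paired t, calibrated to 36 or 37 pairs: 0.67 to 0.70 (28 pairs: 0.80 to 0.81)
- McNemar, assumed difference 0.40 and discordance 0.60: 0.68 to 0.71
- Two proportions with continuity correction, assumed 0.30 versus 0.70: 0.64 to 0.67
- One-sided normal: 0.71 to 0.74

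The range is 0.64 to 0.74, centred near 0.70.

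**Step 4: enrollment needed for 36 pairs per hospital.**
- 50% completion, no later loss: 36/0.50 = 72 (3 × 72 = 216).
- 50% completion, then 15% loss before the three-month questionnaire: 36/(0.50 × 0.85) = 84.7, so 85 (3 × 85 = 255).
- 66.2% completion, no later loss: 36/0.662 = 54.4, so 55 (3 × 55 = 165).

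**Step 5: enrollment achieved, at 50% completion.**
- 88 × 0.50 = 44 pairs and 105 × 0.50 = 52.5 pairs; power about 0.95 and 0.975.
- With a further 15% loss: 88 × 0.50 × 0.85 = 37.4 and 105 × 0.50 × 0.85 = 44.6, both still above 36.

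**Step 6: pooled at the stated minimum.** 129 × 0.50 = 64.5. At 64 pairs and the same effect, power is about 0.99.

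**The case against.** The strongest reply is that the two percentages measure different things. The 50% concerns finishing the whole program, whereas the undefined dropouts might be only those lost between finishing and the later questionnaire. On that reading 43 counts completers, and 100 enrolled at 50% gives 50 of them. The article does not exclude this, but it does not say it either, and the wording fits it poorly: the 50% is applied to participants, the same word used for the 43, and the next sentence sets 43 against expected enrollment. Even if the reading is granted, 43 is not a minimum enrollment, because 43 completers at 50% need 43/0.50 = 86 enrolled.

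Some non-completers might return the questionnaire. The article describes no route for this. At 66.2% completion, a total loss of 15% would need every completer to respond and also 18.8 of the 33.8 percentage points who did not complete.

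Several parts of the reply do stand. The 66.2% is an observed result and does not by itself make a planning assumption inconsistent. The power figures are back-calculated, and from parametric or binary-outcome tests, while the plan is non-parametric. The multiplication in the paragraph is correct; it is the attrition input that does not fit. The article was written in month 18, so replacing 43/129 outright would misreport how the study was planned.

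A reader might infer that the trial is underpowered. The documents do not support this: expected and actual enrollment per hospital both exceed 72 and 85, and the individual-level hypothesis concerns participants without requiring a separate test in each hospital.

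**Conclusion.** The statement is wrong as written, and the matter is minor. At the stated minimum of 43, with the article's own 50% completion, about 21 to 22 pairs remain per hospital instead of 36 to 37, and power for a single-hospital comparison is roughly 70% (64% to 74%) instead of 90%. At 66.2% completion it is about 81%.

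This rests on two assumptions: that course completion limits the pre-post pairs, and that the unstated effect is the one that gives 90% power at 36 to 37 pairs. The exact power depends on the second; the shortfall appears in every variant tried.

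The study as enrolled is not shown to be underpowered. One condition remains: a hospital with 44 completers needs 36/44 = 82% of them to return the later questionnaire to keep 36 pairs, and Results gives only an overall completion rate, not one per hospital.

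**What to change.** Keep 43/129 as the original planning figure and add a correction beside it that:

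1. states that about 36 evaluable pre-post pairs per hospital are needed;
2. defines whether dropouts means failure to finish the course, loss between finishing and the three-month questionnaire, or both;
3. gives the corresponding minimum enrollment: at least 72 per hospital (216 in total) at 50% completion with no later loss, or 85 (255 in total) if the 15% is kept as loss after completion;
4. notes that enrollment of 105, 88 and 88 meets both figures.

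The cost is a few sentences. No further enrollment and no change to the analysis is needed. The summative paper should report pairs analysed per hospital, so that the 36 can be checked directly.
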